#### EBP behaviour

EBP behaviour will be measured in two ways: (1) activity diaries to be provided to all participants, both intervention and waitlist groups, in paper and electronic copies, and (2) frequency of logging in, in the online support for the EBP intervention training participants http://www.unisa.edu.au/cahe/Resources/EBPPhil/default.asp, considered as an electronic EBP learning portfolio. As it is not possible to conduct actual participant observation in practice, activity diaries are commonly used to log and report participants' activities in EBP [37]. The electronic EBP learning portfolio on the other hand, which according to the literature, are both educational intervention and an evaluation strategy," *is the most promising approach to document actual performance of EBP steps *"[37].

The frequency of conducting non-EBP (asking a peer, reviewing a textbook etc) and EBP-related activities (drafting a clinical question in PICO form, searching the literature for the evidence, undertaking critical appraisal and applying the evidence found) will be logged in the activity diaries provided to the participants. The frequency of conducting these activities and the frequency of logging in the online support provided will be counted and interpreted as behaviour measures. Behaviour measures will be interpreted in two ways, evidence-seeking behaviour and practice-change behaviours ref. Activities which relate only to drafting a clinical question, searching and appraising the evidence, are classified as evidence-seeking behaviours. Applying the evidence to an actual patient case is classified as a measure of practice-change behaviour [38].

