## Methods

### Study Aims

There are two aims in this research project:

1. To assess the effectiveness of the EBP training program in improving knowledge, skills, attitudes and behaviour of Filipino physiotherapists; and

2. To provide a tested model of continuing education and uptake of evidence which is contextually relevant to Filipino physiotherapists, and which could be adapted readily for physiotherapists from other developing countries, and allied health professionals who are not first contact practitioners in any health care system.

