#### Procedure

All participants will be asked to answer the Adapted Fresno Test or the AFT [24] for baseline or pre- assessment of their knowledge and skills to EBP, and the Questions on attitudes to EBP [25], for baseline or pre- assessment of their attitudes to EBP (Figure 1). These tools will be sent through the participants' email, the day before the EBP intervention group's scheduled training.

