**Figure 1 F1:**
[figure not shown]
**Flow of procedures**.

The EBP intervention group will attend a one day training (Additional File 1) in a training centre at the University of Santo Tomas, Philippines. The objectives of the training will be provided to the participants before each of the six lectures and the practical sessions. Small group discussions will occur between the lectures, to enhance learning opportunities for participants. A checklist to assist participants to apply the evidence developed for this study will be provided as a take-home recommendation form, to guide the application of evidence in actual patient cases (Figure 2). After the EBP training, a link to an online support will be introduced to the participants. This has been developed to assist the participants in their EBP-related activities post training, as follow up support and multifaceted interventions have more potential to influence clinicians' behaviour to using evidence in practice [2]. This online support is further described in the intervention section of this document. Activity diaries will also be provided to participants to log their EBP-related activities when faced with a new or unique case, and provide their comments to their activities for a period of three months for short term EBP behaviour assessment.

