**Figure 2 F2:**
[figure not shown]
**EBP Checklist**.

At the end of the training, participants will be asked to provide a second set of answers to the Adapted Fresno test and the Questions on attitudes to EBP for post EBP training intervention assessment.

The waitlist control group will undergo the pre and post- knowledge, skills and attitude test at the same period as the intervention group. There will be no training for the control group during this time. However, for the next three months, they will also be provided with activity diaries to log their activities as basis for their treatment when faced with a new or unique case, whether these activities are EBP-related or not.

Three months post EBP training, a third set of answers to the Adapted Fresno test and the Questions on attitudes to EBP, will be obtained from both groups to measure if knowledge, skills and attitudes to EBP were sustained over the three month period in the EBP intervention group and to measure the stability of knowledge, skills and attitudes to EBP of the control group.

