### Plan of analysis

Baseline statistical comparisons will be performed to ensure that all participants from both groups are homogenous and therefore comparable. All post-intervention analyses will be undertaken using an intention to treat approach. Within- and between-group analyses will be undertaken to measure pre and post intervention differences in both intervention and waitlist control group. Changes in outcomes will be compared for both groups using means and 95%Confidence Intervals. Time period for analyses will be pre-intervention, post intervention and three months post intervention.

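### Login counts measure uptake of the intervention rather than its effect on behaviour, and the stated pre/post change analysis cannot be computed for behaviour, which is recorded only after training

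*Protocol article*

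**What the plan says.** Behaviour is one of the domains on which the programme is to be judged. The first Study Aim reads "To assess the effectiveness of the EBP training program in improving knowledge, skills, attitudes and behaviour of Filipino physiotherapists". The Outcomes paragraph and the hypothesis in the Discussion list the same domains, and the hypothesis speaks of gains in each.

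The EBP behaviour section names two measures. Activity diaries go to both arms. The second measure is "frequency of logging in, in the online support for the EBP intervention training participants". Of both together the section says that the frequency of the diary activities and "the frequency of logging in the online support provided will be counted and interpreted as behaviour measures". It then sorts behaviour into evidence-seeking (drafting a question, searching, appraising) and practice-change (applying evidence to a patient). The section on The Intervention describes the online support as belonging to the education package.

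On timing, the Procedure section says of baseline: "All participants will be asked to answer the Adapted Fresno Test or the AFT [24] for baseline or pre- assessment", together with the attitudes questions. It lists no behaviour measure at that point. For the intervention arm, "After the EBP training, a link to an online support will be introduced to the participants". Diaries are handed out at that stage too, "for a period of three months for short term EBP behaviour assessment". Controls take the pre and post tests at the same time without training, and then: "However, for the next three months, they will also be provided with activity diaries to log their activities as basis for their treatment".

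The Plan of analysis gives one scheme for all outcomes: within- and between-group analyses of pre/post differences in both groups, and changes compared using means and 95% confidence intervals. It adds: "Time period for analyses will be pre-intervention, post intervention and three months post intervention". Behaviour is not excepted.

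**The concern.** There are two separate problems.

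First, logging in to the online support is a way of receiving the intervention. A count of logins shows how much of the programme trained participants took up. It does not show whether the programme changed how they practise. Controls do not have the link during the comparison period, so randomisation supplies no comparator for this count. Labelled as a behaviour outcome under an effectiveness aim, ordinary use of the programme could be read as evidence that it works.

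Second, the only analysis stated is of change from before to after training, and neither behaviour measure is recorded before training. An analyst who follows the Plan of analysis literally has nothing to subtract. The choice of what to do instead would then be made after the data are in, for one of the named outcome domains.

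**Working it through.** The protocol gives no numerical figure for behaviour, so there is none to reproduce. The check sets what is collected (Procedure, EBP behaviour) against what the Plan of analysis asks for.

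**Step 1: data available at each planned time point**

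| Measure | Arm | Pre-intervention | Post intervention | Three months |
|---|---|---|---|---|
| Adapted Fresno Test, attitudes | Intervention | yes | yes | yes |
| Adapted Fresno Test, attitudes | Control | yes | yes | yes |
| Activity diary | Intervention | none | none | count over three months |
| Activity diary | Control | none | none | count over three months |
| Logins | Intervention | none | none | count accrued after training |
| Logins | Control | none by design | none by design | none by design |

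Each measure has 2 arms × 3 time points = 6 cells. The test and the attitudes questions fill 6 of 6, diaries fill 2 of 6, and logins fill 1 of 6.

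**Step 2: which planned quantities can be formed**

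Write Y for the measure, I and C for the arms.

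- Within-group change, Y(post) − Y(pre): needs a pre-intervention value. There is none for diaries or logins, so it is undefined in both arms.
- Between-group difference in change, [Y_I(post) − Y_I(pre)] − [Y_C(post) − Y_C(pre)]: undefined for the same reason.
- Change from the immediate post-training point to three months: also undefined, because neither measure has a value at the immediate point.
- Between-group difference at three months, Y_I(3 months) − Y_C(3 months): can be formed for diaries. It cannot be formed for logins, which have no control-arm value.

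So exactly one valid randomised contrast exists for behaviour: the three-month diary comparison. The Plan of analysis does not state it as such, although it does include between-group analysis and a three-month point.

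**Step 3: does a login count represent behaviour as the protocol defines it?**

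The Intervention section lists four uses of the site: reviewing training materials, help with searching through a PICO form, help with appraisal, and queries or feedback. The second and third resemble evidence-seeking. The first and fourth do not match either class. A raw login count cannot separate them. A login made to submit a PICO form could also be entered in the diary, so the same act could be counted under both measures.

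**The case against.** The strongest reply has four parts.

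*No between-arm test of logins is planned.* This stands. The EBP behaviour section assigns diaries to everyone and logins to trained participants, and nothing says that logins will be pooled with diary counts or tested against a control value of zero. A reader might infer that the trial will run a login comparison that is positive by construction, with a type I error close to 100%. That would follow only if such a comparison were made, and the document does not state one. What remains is that logins are called behaviour measures and nowhere limited to uptake or engagement.

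*The dual role is disclosed.* The section does say that such portfolios serve both as teaching and as evaluation, citing a source. Disclosure does not create a comparator or turn exposure into effect.

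*A valid comparison of behaviour exists.* This also stands. A reader might infer that behaviour cannot be analysed at all, or that no valid comparison lies behind any claim about it. The diaries refute that: both randomised arms keep them over the same three months, and randomisation makes a post-training comparison valid without a baseline. The loss is confined to the change analysis.

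*The Plan of analysis is a short summary, and details by outcome belong in a fuller document.* This stands for the choice of model. It does not answer the point in full: a later document cannot supply a baseline that was not collected or control-arm logins, and the article itself fixes the outcome and one pre/post scheme without exception. The word gains in the Discussion need not mean change from baseline, so it is a matter of wording only. Figure 1 is not available here, but the Procedure text places no diary before training.

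**Conclusion.** The point holds, within limits. Logins measure engagement with the intervention in one arm and should not count as a behaviour outcome. The stated pre/post change analysis cannot be computed for either behaviour measure in either arm. The size is structural rather than numerical: one of two behaviour measures has no comparator, and the change analysis is undefined for one of the four named domains (knowledge, skills, attitudes, behaviour). The knowledge, skills and attitudes analyses are unaffected. The plan should be changed, but the flaw does not undermine the design, which already contains the comparison needed.

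The conclusion assumes that no behaviour measure is taken before training and that controls have no access to the online support during the three months; the text supports both. The diary comparison further assumes that both arms record in the same way. The Procedure has the intervention arm log EBP-related activities but asks controls to log activities of either kind, while the EBP behaviour section describes both kinds being logged.

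**What to change.** 1. Move logins out of the behaviour outcomes. Report them descriptively, for the intervention arm only, as engagement with the online support.
2. Define the behaviour outcome as the randomised between-group comparison of three-month diary counts, with evidence-seeking and practice-change analysed separately, using a method suited to overdispersed counts. A negative binomial model is one option among several.
3. Say in the Plan of analysis that the pre/post change analysis applies to the Adapted Fresno Test and the attitudes questions and not to behaviour. Word the behaviour hypothesis as a difference between groups.
4. Keep any rate per new or unique case secondary. Participants identify those cases themselves after randomisation, so training may alter the denominator as well as the numerator.
5. Make the diary instructions identical in both arms.

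The core repair, items 1 to 3, needs only wording and a different analysis for one outcome, with no new data collection; a rate under item 4 would require the diary to record the number of such cases. The downside is one fewer behaviour measure and no within-group change to report for behaviour.

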### Plan of analysis

Baseline statistical comparisons will be performed to ensure that all participants from both groups are homogenous and therefore comparable. All post-intervention analyses will be undertaken using an intention to treat approach. Within- and between-group analyses will be undertaken to measure pre and post intervention differences in both intervention and waitlist control group. Changes in outcomes will be compared for both groups using means and 95%Confidence Intervals. Time period for analyses will be pre-intervention, post intervention and three months post intervention.

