#### Design

The EBP training program will be tested using a randomised controlled design, using a waitlist control group.

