#### Sample Size determination

To detect a "moderate" effect size (0.6) at 80% power and 5% level of significance (2 tailed distribution), the required sample size for each group (intervention and control) is 27 physiotherapists (calculated using standard sample size calculator software in MedCalc). We will test for a conservative (moderate) effect in our RCT, as we are uncertain whether the large effect size from the pilot study was an artefact of the small sample, or an example of a Hawthorne effect.

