### Outcome measures

#### EBP knowledge and skills

The Adapted Fresno Test will be used to measure EBP knowledge and skills. The test was adapted by McCluskey and Bishop [24] from the original Fresno test used in medicine by Ramos et al [35], and has been reported to have acceptable psychometric properties, in measuring change in knowledge and skills to EBP among novice rehabilitation professionals. The test consists of seven questions which address EBP competencies relevant to health practitioners. There are two versions of the test (different clinical scenarios for each test) and ICC scores for subtests were, Version 1: ICC, 0.80-0.96; Version 2: 0.68-0.94 and ICC for total scores were Version 1: ICC, 0.96; Version 2: ICC, 0.91. Internal consistency was acceptable (Cronbach's alpha = 0.74). For our study, version 1 was used for baseline assessment and version 2 for post training assessment. This choice was made to avoid any potential practice effect (defined as "*improvements in cognitive test performance due to repeated evaluation with the same test materials*"). Such practice effects can be a source of error [36].

Inter-tester reliability was assessed among the researchers participating in this study as part of the pilot study of the training program, and acceptable reliability was found (ICC 0.99) for both versions.

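### The planned comparison of changes between groups is valid but less efficient than adjusting for the baseline score, within-group analyses stand level with it, and baseline tests cannot ensure comparability

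*Protocol article*

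**What the plan says.** The Plan of analysis section makes three statements that bear on this point.

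- On baseline: "Baseline statistical comparisons will be performed to ensure that all participants from both groups are homogenous and therefore comparable".
- On the analyses: "Within- and between-group analyses will be undertaken to measure pre and post intervention differences in both intervention and waitlist control group".
- On the comparison: "Changes in outcomes will be compared for both groups using means and 95%Confidence Intervals".

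The time points are before training, after training and three months later, under intention to treat. Neither the within-group nor the between-group analysis is named as the one that decides effectiveness, and no baseline covariate is mentioned.

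Under Procedure, both arms complete the Adapted Fresno Test (AFT) and the attitude questions at baseline, post-training and three months. Under EBP knowledge and skills, the AFT form changes between the first two occasions: "version 1 was used for baseline assessment and version 2 for post training assessment". The Sample Size determination section assumes an effect of 0.6, 80% power and two-sided 5%, and concludes that "the required sample size for each group (intervention and control) is 27 physiotherapists".

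**The concern.** There are three separate weaknesses in what the section states.

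1. **Change scores.** Subtracting baseline gives it a fixed weight of one. ANCOVA estimates the weight from the data. With equal variances the change score is never more precise (apart from one degree of freedom), and for r below 0.5 it is less precise than ignoring baseline altogether. It also over-corrects a chance imbalance. If the intervention arm starts D higher, the expected difference in change is the effect minus (1 − r)D.
2. **Within-group analyses on an equal footing.** A pre-post gain in one arm mixes the training effect with retesting and with any difference in difficulty between the two AFT versions. Only the contrast between arms removes these.
3. **Baseline tests as assurance.** Under proper randomisation any baseline difference is due to chance, so a test of it answers no useful question. A non-significant result in a small trial does not show that the groups are alike.

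What is at stake is precision in a small trial, and clarity about which result carries the conclusion.

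**Working it through.** **Inputs from the article.** Two groups; effect 0.6; two-sided 5%; 80% power; 27 per group; no dropout allowance stated.

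**Inputs assumed.** The correlation r is not given, so a range of 0.3 to 0.8 is used. The article does not say which SD defines 0.6, so both readings are shown. Baseline and follow-up variances are taken as equal.

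**The plan's own figure.** An unadjusted comparison of two means needs n = 2(1.96 + 0.842)² / 0.6² = 43.6, so 44 per group (45 by the t-test). The stated 27 is not reproduced. With 27 per group the t-test has 58% power for 0.6.

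**Variances, in units of the score variance.**
- Change score: 2(1 − r)
- ANCOVA: 1 − r²
- Ratio of ANCOVA to change score: (1 − r)(1 + r) / [2(1 − r)] = (1 + r)/2

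**Power, 0.6 in SDs of the score.** Noncentral t with noncentrality 0.6 / (SD × √(2/27)); 52 degrees of freedom for the change score, 51 for ANCOVA. Example at r = 0.5: the change-score SD is 1, so noncentrality is 0.6/0.272 = 2.20 and power is 58%. The ANCOVA SD is √0.75 = 0.866, so noncentrality is 2.55 and power is 70%.

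| r (assumed) | Variance ratio | Change score | ANCOVA |
|---|---|---|---|
| 0.3 | 0.65 | 45% | 62% |
| 0.5 | 0.75 | 58% | 70% |
| 0.6 | 0.80 | 68% | 77% |
| 0.7 | 0.85 | 80% | 86% |
| 0.8 | 0.90 | 93% | 95% |

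The gain runs from about 17 points down to about 2. ANCOVA with 27 per group reaches 80% only from r of about 0.62 (normal approximation) or 0.64 (noncentral t).

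**Power, 0.6 in SDs of the change.** The change score has 58% at any r. The ANCOVA SD is √((1 + r)/2) change SDs, giving 77%, 70% and 65% at r = 0.3, 0.5 and 0.7. ANCOVA is ahead on both readings, but here its advantage shrinks as r rises.

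**Baseline tests.** With 27 per group, a two-sided 5% t-test has 80% power only for a difference of about 0.78 SD, so smaller but material imbalances would often pass. In the other direction, six variables could be tested: age, gender, years in practice, education, AFT and attitudes. If they were independent, the chance of at least one false signal is 1 − 0.95⁶ = 26%.

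**The case against.** The strongest reply is that a between-group comparison with confidence intervals, under intention to treat, is already planned. It is unbiased under randomisation. A condensed article may also leave the model to a fuller plan, and change analysed with the baseline score as covariate gives the same treatment effect as ANCOVA. This stands in part: missing model detail is not the complaint. The comment rests on what the section does state, and offers an improvement that uses data already collected.

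Two further replies are fair. Within-group analyses have a stated purpose under Procedure: whether gains last in the trained arm and whether the control arm is stable. A reader might infer that effectiveness will be judged from a significant gain in one arm and none in the other. The article does not say so; it only fails to say which analysis decides. Likewise, no action is attached to the baseline comparisons, so the 26% figure describes noise and not a biased estimate.

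A reader might also infer that adjustment would recover much of the power that 27 per group lacks. The article does not support that. It gives neither r nor the SD behind 0.6, and two AFT versions may lower r. With 0.6 in score SDs, ANCOVA reaches only 62% at r = 0.3, close to the 58% from ignoring baseline. At r = 0.7 the change score already has 80%.

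**Conclusion.** The point holds as a matter of efficiency and wording; the planned comparison is not invalid. Adjusting for baseline is at least as precise as comparing changes, and at 27 per group is worth about 2 to 17 points of power for r from 0.8 down to 0.3, with 0.6 in score SDs. These sizes rest on an assumed r and equal variances. The direction does not depend on which SD defines 0.6. Adjustment does not repair the sample-size figure, which is a separate matter.

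The sentence on baseline comparisons claims something such tests cannot deliver, and the section leaves open which analysis carries the conclusion.

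The scope is the AFT, and the attitude questions if a total score is used; the article describes seven three-point items and no total. It does not extend to behaviour: Procedure lists no baseline diary measure, and log-ins are counted only in the trained group.

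**What to change.** In the Plan of analysis:

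- Name as the effectiveness analysis for the AFT the between-group difference at post-training and at three months, adjusted for the baseline score, with 95% CI. Use ANCOVA at each time, or a mixed model with arm, time and arm-by-time. Do the same for attitudes if a total score is used.
- Fix any further covariates in advance, not from baseline tests.
- Present within-group changes as descriptive only, and note the change of AFT version.
- Replace the sentence on baseline comparisons with a descriptive table by group, without tests.
- State that the adjustment does not apply to the diary and log-in outcomes.

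The cost is a rewording of one section before outcomes are seen. No new data, visits or participants are needed.
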